## Abstract

**Background:**

Prior studies have shown that intermittent fasting is capable of producing improvements in body weight and fasted health markers. However, the extent to which intermittent fasting incurs compensatory changes in the components of energy balance and its impact on postprandial metabolism are yet to be ascertained.

**Methods:**

A total of 30–36 lean participants and 30–36 overweight/obese participants will be recruited to provide two separate study groups who will undergo the same protocol. Following an initial assessment of basic anthropometry and key health markers, measurements of habitual energy intake (weighed food and fluid intake) and physical activity energy expenditure (combined heart rate and accelerometry) will be obtained over 4 weeks under conditions of energy balance. Participants will then be randomly allocated to one of three experimental conditions for 20 days, namely (1) daily calorie restriction (reduce habitual daily energy intake by 25%), (2) intermittent fasting with calorie restriction (alternate between 24-hour periods of fasting and feeding to 150% of habitual daily energy intake), (3) intermittent fasting without calorie restriction (alternate between 24-hour periods of fasting and feeding to 200% of habitual daily energy intake). In addition to continued monitoring of energy intake and physical activity during the intervention, participants will report for laboratory-based assessments of various metabolic parameters both before and after the intervention. Specifically, fasting and postprandial measurements of resting metabolic rate, substrate oxidation, appetite, food preference, and plasma concentrations of key metabolites and hormones will be made, in addition to subcutaneous abdominal adipose tissue biopsies in the fasted state and an assessment of body composition via dual-energy x-ray absorptiometry.

**Discussion:**

Comparing observed changes in these measures across the three intervention arms in each group will establish the impact of intermittent fasting on postprandial metabolism and the components of energy balance in both lean and overweight/obese populations. Furthermore, this will be benchmarked against current nutritional interventions for weight management and the relative contributions of negative energy balance and fasting-dependent mechanisms in inducing any observed effects will be elucidated.

**Trial registration:**

Trial retrospectively registered at clinicaltrials.gov under reference number NCT02498002 (version: IMF-02, date: July 6, 2015).

**Electronic supplementary material:**

The online version of this article (10.1186/s13063-018-2451-8) contains supplementary material, which is available to authorized users.

## Background

Intermittent fasting (IMF) is a dietary strategy in which periods of normal food and drink consumption are punctuated by periods of energy restriction or fasting. The objective of IMF is to create a net reduction in energy intake that causes it to fall below energy expenditure, thereby creating a state of negative energy balance and inducing weight loss [1]. Work by various groups has consistently shown that such an approach is associated with significant reductions in body mass in obese participants, whilst also improving blood lipid profile and lowering concentrations of inflammatory markers [2–4]. Although these findings are broadly comparable to those seen following a period of daily calorie restriction [5–13], current understanding of how IMF affects human health and metabolism is far from complete.

Firstly, while the weight losses reported in prior studies of IMF reflect a state of negative energy balance, the precise changes that occur in the components of energy balance have not been characterised. This is of importance as prolonged periods of daily calorie restriction, which also aim to create a state of negative energy balance, elicit compensatory reductions in energy expenditure and increases in appetite that preserve body fat stores and undermine weight loss efforts [14–22]. Although this adaptive phenomenon has been thoroughly documented in studies of daily calorie restriction, there is no evidence to suggest that such a mechanism is invoked in response to IMF. Changes in leptin concentration, a proposed hormonal regulator of energy balance [23], have been shown to be similar between IMF and daily calorie restriction [2, 4, 11, 24]. However, this does not seem to translate to measurable changes within the components of energy balance, with studies failing to detect corresponding reductions in resting metabolic rate [25] or habitual physical activity [26]. Although promising, these prior studies have focused on isolated aspects of energy expenditure that do not accommodate the complex interplay between the components of energy balance [1, 21], thus warranting closer examination.

Secondly, reductions in fasting insulin concentration have been consistently shown in response to various IMF interventions as reviewed by Barnosky et al. [8]. This review also highlights that, in a subset of these studies, fasted indices of insulin resistance generally improve following a period of IMF. However, it is important to note that these fasted measurements can often overlook subtle modifications in glucose metabolism under dynamic conditions [27] such as those seen in the postprandial period. At present there is a dearth of knowledge on how IMF impacts postprandial metabolism which needs to be addressed, especially upon considering that Western cultures spend the majority of their waking time in a postprandial state [28]. Furthermore, discerning the relative contributions of fasting and negative energy balance to any observed changes in metabolism carries substantial implications for how obesity and the associated comorbidities are treated, as it has been suggested that temporal modifications in energy intake exert independent influences on metabolic health [29–32].

With over 50% of the adult population in the UK currently classified as overweight or obese [33], accompanied by an increased risk of type 2 diabetes and cardiovascular disease, finding more effective strategies to manage these conditions remains imperative [34]. Although the limited body of prior literature offers promising insights as to the efficacy of IMF in improving metabolic health, numerous uncertainties remain. As such, the present study has three core objectives that will be separately addressed in both a lean cohort and in an overweight/obese cohort.

The study will aim (1) to establish whether IMF elicits compensatory changes in the components of energy balance and compare these against the changes arising from a daily calorie restriction intervention; (2) to examine the effect of IMF on postprandial metabolism relative to a daily calorie restriction intervention; and (3) to explore whether IMF impacts upon postprandial metabolism and the components of energy balance independently from chronic energy imbalance by contrasting against a eucaloric IMF intervention.

## Methods

### Participants

To address these objectives two separate cohorts of 30–36 healthy adults who satisfy the inclusion/exclusion criteria outlined below will be recruited. One cohort will feature exclusively lean participants (body mass index (BMI) 20.5–25.0 kg/m^2^) and the other overweight/obese participants (BMI > 25.0 kg/m^2^). This will be confirmed using the fat mass index (FMI) obtained from a dual-energy x-ray absorptiometry (DEXA) scan, with values ≤ 7.5 kg/m^2^ and ≤ 11.0 kg/m^2^ classified as lean for males and females, respectively. In line with the objectives of this protocol the effects of IMF in these two cohorts will not be compared, instead they will be published as separate studies with matched methods to provide a thorough evaluation of the impacts of IMF in these two metabolically distinct populations.

Participants in each cohort shall then be allocated to one of three parallel intervention arms in a 1:1:1 allocation ratio using a stratified randomisation scheme. This will feature a factor for objectively measured physical activity level (PAL), which is calculated by dividing each participant’s total daily energy expenditure by their resting metabolic rate, to ensure an even distribution of lower activity (PAL < 1.75) and higher activity (PAL ≥ 1.75) participants in each condition. In accordance with best practice recommendations for randomised controlled trials [35], allocation concealment will be employed to minimise bias. The scheme will be generated by a senior author who is not involved in participant recruitment or management ([name]) using an electronic random number generator. Intervention allocation will be requested via email by those responsible for participant management (IT), with only the participant code, BMI/FMI and PAL being sent. As only the delivery team will engage with participants and know their corresponding code, whilst only the senior author knows the block sizes and sequences, it is not possible for the allocation to be reliably predicted or biased by either party. Full details of the overall randomisation scheme will be included in publications once all allocations are completed in order to prevent deciphering [36]. The protocol for these studies has received ethics approval from the National Health Service Research Ethics Committee (reference: 15/SW/0007) and has been registered at clinicaltrials.gov under reference number NCT02498002 (version: IMF-02, date: July 6, 2015).

#### Inclusion

Participants (1) aged 18–65 years, (2) with a BMI of 20.5–25.0 kg/m^2^ (lean) or > 25.0 kg/m^2^ (overweight/obese), (3) a stable body weight (±3 kg) for at least 6 months [37], (4) able and willing to comply with study procedures, (5) willing to undertake required fasting durations, and (6) with the capacity to provide informed consent will be included in the study.

#### Exclusion

Participants (1) with body weight > 120 kg, (2) recent or planned engagement in fasting practices (within 3 months of start date), (3) recent or planned change in diet/physical activity habits, (4) suffering from an eating disorder as assessed using the Eating Disorder Examination Questionnaire (EDE-Q 6.0) [38], (5) diagnosed with diabetes or other metabolic health disturbances, (6) with an ongoing medical condition or treatment that may interfere with study variables, (7) menopausal, (8) pregnant, recently pregnant, planning to become pregnant (within 3 months) or currently breastfeeding, (9) having donated blood within last 3 months, (10) with a lack of capacity/language skills to independently follow the protocol, (11) who cannot consume test meals due to intolerances/dietary preferences (i.e. vegan, gluten, milk proteins), or (12) with any other behaviour or condition that may introduce bias to the study or poses undue personal risk, will be excluded from the study.

### Power calculation

The sample size for this study has been estimated using an a priori power analysis of studies employing similar durations of daily calorie restriction. Specifically, Friedlander et al. [39] observed a significant decline in resting metabolic rate following 21 days of daily calorie restriction (pre: 1898 ± 262 kcal/day, post: 1670 ± 203 kcal/day). Applying a two-tailed *t* test to these data suggests that 11 participants would be required to achieve 80% power when detecting such an effect at an alpha level of 0.05. Focusing instead on changes in postprandial glucose metabolism, Molfino et al. [40] reported a significant reduction in 2-hour post-bolus plasma glucose values during an oral glucose tolerance test following 10 days of daily calorie restriction (pre: 10.72 ± 3.56 mmol/L, post: 7.10 ± 2.96 mmol/L). In this instance, nine participants would be required to detect a comparable within-treatment effect with 80% power at an alpha level of 0.05. Collectively, this suggests that 9–11 participants will be required per group to establish within-treatment effects in the primary outcomes. However, given the potential for variability in the outcomes of interest, particularly when working with obese populations [16, 17], a more conservative requirement of 10–12 was decided upon. With 10–12 participants required in each of the three intervention arms, 30–36 lean participants and 30–36 overweight/obese participants will be sought in total, allowing examination of these two metabolically distinct populations to be kept separate. Recruitment will be conducted using adverts at local employers and media outlets, and will proceed on a rolling basis until an adequate sample size is reached. To minimise loss to follow-up emphasis will be placed on considering the demands of the study before enrolling and that feedback of personal results will only be available to those who complete all three lab sessions. In cases of withdrawal, additional participants will be sought to maintain statistical power; however, the point of withdrawal and the accompanying reason will be reported in a CONSORT flow diagram in subsequent publications.

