### Data analysis

As outlined in the aims of the present study, the primary outcomes will explore the effects of the intervention on postprandial glucose/insulin responses (pre–post) and energy balance – reflected by changes in resting metabolic rate (pre–post), physical activity energy expenditure (monitoring–intervention) and postprandial thermogenesis (pre–post). Secondary outcomes will explore changes from pre- to post-intervention in body composition, substrate oxidation, lipid profile, leptin concentration, c-reactive protein concentration, adipose tissue gene expression, postprandial lipaemia and postprandial appetite regulation/perception. In addition, differences in physical activity intensity and dietary composition between the monitoring and intervention phases will be examined. As it is not the objective of this study to compare these differences between the cohorts, two sets of analyses will be conducted on a per protocol basis -– one for the lean cohort and one for the overweight/obese cohort. Both will centre upon a two-way mixed model analysis of variance featuring a factor for diet allocation and a factor for time-point. This will permit an examination of the effect of each diet on the outcomes of interest (i.e. pre vs. post/monitoring vs. intervention) and whether this effect varied between the three dietary conditions. Pre-existing differences between groups at baseline will be examined using a one-way analysis of variance featuring a factor for diet allocation. Significant differences emerging from these tests will be explored using appropriate post-hoc tests to adjust for multiple comparisons and isolate the source(s) of variance. In addition to these analyses at the group level, individual responses will also be closely scrutinised to examine whether outliers could be affecting the interpretation. Further analysis, such as sub-group analysis, may also be conducted in light of patterns emerging in the final dataset. Baseline characteristics of participants who withdraw during the intervention will also be compared against the final population using *t* tests. Statistical significance will be accepted at *P* < 0.05.

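### The sample size is stated for the primary outcomes as a set, but calculations are reported for only two of them, and the lower ends of both ranges fall below the protocol's own figure of 11 for resting metabolic rate

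*Protocol article*

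**What the plan says.** The Data analysis section of the protocol article sets out the primary outcomes: "the primary outcomes will explore the effects of the intervention on postprandial glucose/insulin responses (pre–post) and energy balance". Energy balance is represented by resting metabolic rate, "physical activity energy expenditure (monitoring–intervention) and postprandial thermogenesis (pre–post").

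The Power calculation section reports two calculations, both from published studies of daily calorie restriction:

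- Resting metabolic rate ("pre: 1898 ± 262 kcal/day, post: 1670 ± 203 kcal/day"), from which "11 participants would be required to achieve 80% power when detecting such an effect at an alpha level of 0.05", using a two-tailed t test.
- Two-hour glucose in an oral glucose tolerance test ("pre: 10.72 ± 3.56 mmol/L, post: 7.10 ± 2.96 mmol/L"), from which "nine participants would be required to detect a comparable within-treatment effect with 80% power at an alpha level of 0.05".

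It then generalises: "Collectively, this suggests that 9–11 participants will be required per group to establish within-treatment effects in the primary outcomes". The next sentence raises the requirement to 10–12 per arm because outcomes may be variable, particularly in obese participants. No figure accompanies that step.

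**The concern.** The generalising sentence is wider than its support in two respects.

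First, it speaks for the primary outcomes as a set, while inputs are shown for two measures. Insulin, physical activity energy expenditure and postprandial thermogenesis have no reported effect size, SD or power. The last two are two of the three expenditure components listed for the trial's first aim, which concerns compensatory changes in energy balance.

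Second, when separate calculations give 11 and 9, the number that serves both is 11. A range that starts at 9, or at 10 after the increase, starts below the protocol's own requirement for resting metabolic rate.

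What is at stake is how null results are read. A non-significant change in activity expenditure or thermogenesis could be taken to come from a test with 80% power, which nothing in the article establishes.

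**Working it through.** **Inputs.** Means, SDs, two-sided alpha of 0.05 and 80% power are from the Power calculation section. Sidedness is stated for resting metabolic rate and taken to be the same for glucose. The pre–post correlation r is not given and has to be assumed.

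**Formulas.** SD of change = √(s₁² + s₂² − 2·r·s₁·s₂); dz = mean change / SD of change. Power comes from the noncentral t distribution with n − 1 degrees of freedom and noncentrality dz·√n.

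**Step 1: reproduce the stated figures, with r = 0.5.**

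- Resting metabolic rate: change 1898 − 1670 = 228 kcal/day. SD of change = √(262² + 203² − 262 × 203) = √56,667 = 238.0. dz = 228 / 238.0 = 0.958. Smallest n with at least 80% power: **11**, as stated.
- Glucose: change 10.72 − 7.10 = 3.62 mmol/L. SD of change = √(3.56² + 2.96² − 3.56 × 2.96) = √10.898 = 3.30. dz = 3.62 / 3.30 = 1.097. Smallest n: **9**, as stated.

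Dividing by the pooled SD instead gives dz of 0.973 and 1.106, and the same 11 and 9. An independent-samples t test would need 18 and 14 per group, so the stated figures are paired, within-arm numbers.

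**Step 2: how far this depends on r.** As r goes from 0 to 0.9, the required n runs from 19 to 5 for resting metabolic rate and from 15 to 4 for glucose. The stated 11 pins r down closely. It needs dz of at least 0.938 (the value with 80% power at n = 11) but below 0.996 (the value at n = 10). Those correspond to SDs of change of 228 / 0.938 ≈ 243 and 228 / 0.996 ≈ 229. With r = (262² + 203² − SD²) / (2 × 262 × 203), r lies between about 0.48 and 0.54.

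**Step 3: power across the stated ranges, with r = 0.5.**

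| n per arm | Resting metabolic rate | 2-hour glucose |
|---|---|---|
| 9 | 71% | 82% |
| 10 | 77% | 87% |
| 11 | 82% | 91% |
| 12 | 85% | 93% |

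Glucose reaches 80% throughout. Resting metabolic rate does not at 9 or 10. Across the r values that give 11 (0.48 to 0.54), power at n = 10 runs from about 75% to just under 80%. It cannot reach 80% if 11 is the smallest adequate number.

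**Step 4: what 10–12 per arm offers the outcomes with no reported calculation.** No required n can be computed, because the article gives no inputs. The smallest within-arm change detectable with 80% power, in SDs of the change, is:

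| n per arm | Detectable dz |
|---|---|
| 10 | 1.00 |
| 11 | 0.94 |
| 12 | 0.89 |

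For scale, with assumed values of dz:

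| Assumed dz | Power at 10–12 per arm | n needed for 80% |
|---|---|---|
| 0.8 | 62–71% | 15 |
| 0.5 | 29–35% | 34 |

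These dz values are illustrations, not estimates for any of the three outcomes.

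**The case against.** **Sizing on selected primary outcomes is common.** The protocol has two primary domains, glucose/insulin responses and energy balance, and it sizes one measure from each. That is a fair reading, and if glucose and insulin are counted together there are four primary outcomes, not five. It defends the choice of inputs. It does not defend a sentence that extends the result to the primary outcomes generally.

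**The size adopted is 10–12, not 9–11.** This stands, and it makes the n = 9 figures relevant only to the generalising sentence. The increase carries no figure, however, and its lower end is still below 11.

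**The detectable-change figure is not the power of the planned analysis.** The Data analysis section plans a mixed-model analysis of variance with post-hoc tests adjusted for multiple comparisons. The 0.9–1.0 SD figure comes from an unadjusted paired test and should be labelled so.

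**The glucose input is indirect.** It is an oral glucose tolerance value, while the trial gives mixed meals (Meal tests section). This stands, and is a reason to name the calculated outcome exactly.

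Four stronger readings are tempting, and the article does not support them:

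- *That 80% power is claimed for both calculated outcomes at once.* The sentence combines two separate results into a range. Neither it nor the analysis plan requires both to be significant, so joint power is not at issue.
- *That the Background marks physical activity as especially underpowered.* It describes earlier fasting studies as "failing to detect corresponding reductions in resting metabolic rate [25] or habitual physical activity [26"]. The same is said of resting metabolic rate.
- *That no calculation was ever made for the other outcomes.* A journal article can show only that none is reported in it.
- *That the sample size arithmetic is wrong.* Both figures reproduce.

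**Conclusion.** The concern holds as a matter of what is claimed. The article extends its sample size to the primary outcomes while reporting a basis only for resting metabolic rate and 2-hour glucose. The lower ends of both ranges contradict its own 11: power for resting metabolic rate is about 71% at 9 per arm and 77% at 10. That a size below 11 falls short follows from the protocol's own figure. The exact percentages rest on r of about 0.5, which the article does not state but which its 11 and 9 imply.

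A reader might infer that the trial is underpowered for insulin, activity expenditure and thermogenesis. That does not follow. Without an effect size or SD their power is unknown; what is known is the detectable change of about 0.9–1.0 SD of the change at 10–12 per arm. Nor can that threshold be put into kcal/day, since the article gives no SD of change for activity expenditure. The shortfall at 10 per arm is small and disappears at 11.

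**What to change.** Restate the conclusion of the Power calculation section to say that:

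- 80% power applies to the change in resting metabolic rate (at least 11 per arm) and in 2-hour oral glucose tolerance test glucose (at least 9 per arm), each taken singly, with the assumed pre–post correlation (about 0.5 reproduces both);
- 10 per arm gives slightly under 80% for resting metabolic rate (about 77% at that correlation);
- no calculation is reported for insulin, physical activity energy expenditure or postprandial thermogenesis, and 10–12 per arm gives 80% power there only for within-arm changes of about 0.9–1.0 SD of the change, from an unadjusted paired test.

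If the authors hold calculations for those outcomes, reporting them with their assumptions would serve equally well. Otherwise, carry the detectable-change figure into the results papers, so that non-significant findings on the three outcomes are read against it.

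The cost is wording and a slightly less favourable statement of power. No participants or procedures are added. The Trial status section reports recruitment as ongoing, so the change could be made before results are known.

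### The adopted 10–12 per arm starts below the protocol's own requirement of 11 for resting metabolic rate, and the sizing uses an unadjusted alpha although adjusted post-hoc tests are planned

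*Protocol article*

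**What the plan says.** All of the sizing is in the protocol article under Power calculation. For RMR it takes a cited calorie-restriction study ("pre: 1898 ± 262 kcal/day, post: 1670 ± 203 kcal/day"), applies a two-tailed t test, and concludes that this "suggests that 11 participants would be required to achieve 80% power when detecting such an effect at an alpha level of 0.05". For 2-hour glucose ("pre: 10.72 ± 3.56 mmol/L, post: 7.10 ± 2.96 mmol/L") it obtains nine on the same terms. It sums these up as 9–11 per group for within-treatment effects. Then, citing possible variability, particularly in obese populations, it states that "a more conservative requirement of 10–12 was decided upon". Three arms give 30–36 per cohort. Recruitment "will proceed on a rolling basis until an adequate sample size is reached", and withdrawals are replaced.

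Data analysis lists RMR and postprandial glucose/insulin among the primary outcomes. It plans a diet-by-time mixed ANOVA in each cohort, with significant differences followed up by "appropriate post-hoc tests to adjust for multiple comparisons". The method of adjustment is not named.

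**The concern.** A margin for extra variability should put the whole adopted size at or above the derived requirement. Here the range moves up by one at each end, from 9–11 to 10–12, so a cohort of 30 meets the plan while falling one per arm short of the number the plan says RMR needs. The stated 80% is then not met at every size that the plan accepts.

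The sizing also treats each within-arm test as a single test at 0.05, although the analysis section says that follow-up tests will be adjusted. The power quoted is therefore for a more lenient test than the one planned. An unremarkable RMR result in one arm could be read as evidence of no metabolic compensation when the study had a sizeable chance of missing it.

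**Working it through.** **Inputs (Power calculation).** RMR: difference 1898 − 1670 = 228 kcal/day, SDs 262 and 203. Glucose: difference 10.72 − 7.10 = 3.62 mmol/L, SDs 3.56 and 2.96. Two-tailed, alpha 0.05, power 80%. The pre–post correlation r is not given and has to be assumed.

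**Formulas.** SD of change = √(s₁² + s₂² − 2·r·s₁·s₂); dz = difference / SD of change. Power is the chance that a noncentral t with n − 1 degrees of freedom and noncentrality dz·√n exceeds the two-sided critical value.

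**Reproducing the protocol's figures, r = 0.5.**
- RMR: √(68644 + 41209 − 53186) = √56667 = 238.05; dz = 228 / 238.05 = 0.958. Smallest n for 80%: 11.
- Glucose: √(12.6736 + 8.7616 − 10.5376) = √10.8976 = 3.30; dz = 3.62 / 3.30 = 1.097. Smallest n: 9.

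Both stated figures are returned. At r = 0.5 a one-sided paired test would give 9 and 7, and an independent two-sample test 18 and 14 per arm, so a two-sided paired test is the natural reading. Values of r from about 0.48 to 0.54 return both 11 and 9.

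**Power at the adopted sizes, unadjusted, separate paired tests, r = 0.5.**

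| n per arm | RMR: dz·√n | critical t | RMR power | Glucose power |
|---|---|---|---|---|
| 10 | 3.03 | 2.262 | 76.9% | 86.9% |
| 11 | 3.18 | 2.228 | 81.6% | 90.5% |
| 12 | 3.32 | 2.201 | 85.5% | 93.2% |

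Over r = 0.48–0.54, RMR power at n = 10 runs from 75% to just under 80%. It cannot reach 80% for any r that returns 11, because 11 is then the smallest n that does.

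**Does the margin cover the variability given as its reason?** If the SD of change is 10% larger (238.05 × 1.1 = 261.9), RMR power is 69% at n = 10 and 78% at n = 12.

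**Power after adjustment.** Assumptions: Bonferroni over three (0.05 / 3 = 0.0167) and r = 0.5. Two readings of the post-hoc test are possible: a separate paired test in each arm (n − 1 degrees of freedom), or a contrast using the ANOVA's pooled within-subject error (3(n − 1) = 27, 30 or 33 degrees of freedom, assuming equal SD of change across arms).

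| n per arm | RMR, separate | RMR, pooled | Glucose, separate | Glucose, pooled |
|---|---|---|---|---|
| 10 | 56.1% | 68.2% | 69.6% | 81.3% |
| 11 | 62.7% | 73.6% | 76.1% | 85.7% |
| 12 | 68.7% | 78.2% | 81.5% | 89.2% |

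At r = 0.5, 80% adjusted power for RMR needs 15 per arm with separate tests or 13 with pooled error. The result depends on r: at r = 0.54, the top of the range that fits the protocol, adjusted RMR power at n = 12 is 73% separate and 82% pooled.

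**The case against.** The shortfall at n = 10 is about three percentage points, on one outcome, at one end of the range. Glucose exceeds 80% unadjusted throughout. If unadjusted contrasts used the ANOVA's pooled error, RMR power would be 83.1% even at n = 10, and at r = 0.6 a separate paired test gives 84.8%. All of this is correct and keeps the point modest. It does not remove the inconsistency: the protocol derived 11 by its own method and then accepted 10, and r = 0.6 does not return 11.

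The choice of post-hoc method is commonly left to the analysis plan, which is not shown. So no single adjusted figure can be held against the protocol. A reader might infer that adjusted RMR power is simply 56% and that 15 per arm are needed. The text does not support that, because it names neither Bonferroni, nor a count of three, nor separate tests. A correlation of 0.7 would give 79.2% at n = 10 even with separate tests, although it too fails to return 11. What stands is that the sizing alpha and the stated intention to adjust do not match.

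A reader might also infer that an unfixed total in an unblinded study inflates the type I error. Testing one outcome at 10, 11 and 12 per arm and closing on significance would take 5% to about 7.7%, but that is hypothetical. The protocol plans no such looks. Data management disclaims ending the trial early on interim results and places manuscript drafting after a complete dataset is compiled, and blood samples are frozen for later analysis. Knowing allocation is not the same as comparing outcomes by arm. The text leaves the closing number open between 30 and 36 per cohort; it does not show data-driven stopping.

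**Conclusion.** The point holds in two parts, and it is worth correcting although it is not grave.

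First, the lower end of the adopted range is below the requirement derived in the same section. On the test that reproduces the protocol's figures, RMR power at 10 per arm is 75% to just under 80% (77% at r = 0.5), so calling the range more conservative is not justified at that end. This rests only on the protocol's own 11.

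Second, the quoted 80% is for unadjusted tests, while adjusted ones are planned. Under Bonferroni over three and r = 0.5, RMR falls short of 80% across 10–12 per arm on either reading of the error term. Glucose reaches 80% only at 12 per arm with separate tests, and throughout with pooled error. The size of this part depends on the assumed adjustment, error term and correlation.

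The stated figures of 11 and 9 are not themselves wrong.

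**What to change.** Set the target at 36 evaluable participants per cohort, 12 per arm, and state that each cohort closes at that number with no outcome comparison by arm beforehand. Restate RMR power at 12 per arm as about 85.5% unadjusted and about 69–78% adjusted, naming the assumptions (r = 0.5, Bonferroni over three, separate or pooled error). If 10 per arm is kept as a minimum, state its power (about 77% unadjusted, 56–68% adjusted) and drop the description as more conservative.

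This removes the inconsistency and settles the closing number. It discloses the multiplicity shortfall for RMR without curing it, since 12 per arm is still below the 13–15 computed above. The cost is small: wording, at most 36 − 30 = 6 more participants per cohort than the current minimum, all within the planned range, and a less favourable stated power. The Trial status section says that recruitment was still ongoing, so the target could still be fixed at that stage.
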